### Statistical analysis

Statistical analyses will be performed using SAS version 9.1.3 (SAS Institute Inc. Cary NC) and R version 2.8.1 (R Foundations for Statistical Computing). All statistical tests will be two-tailed and a 5% significance level maintained throughout the analyses. All treatment evaluations will be performed on the principle of Intention to Treat (ITT). Repeated measures analysis using the mixed model will be carried out to evaluate the effect of intervention on change from baseline measures at 12 and 24 weeks, adjusting for baseline outcome measure, age (in years), sex (male/female), and ethnicity (Māori/Pacific/nMnP). With roughly equal number of Māori, Pacific and non-Māori non-Pacific participants, appropriate sub-group analysis will be carried out for each ethnicity if there is a significant overall treatment effect.

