### Sample size

A sample size of 330 participants was estimated to provide at least 90% power at 5% level of significance (two-sided) to detect a 0.8 kg/m^2 ^difference in change in BMI from baseline to the end of intervention period between the two groups, assuming a standard deviation (SD) of 2.0 kg/m^2 ^and allowing for 20% loss to follow up. The estimated difference in BMI assumed a difference in weight between groups at the end of intervention of approximately 2 kg with an average height of 1.58 m. This sample size also provides at least 90% power to detect an estimated 3–5 ml/kg/min difference in peak VO_2max _assuming a SD of 7 ml/kg/min. Recruitment of equal numbers of Māori (indigenous people) (n = 110), Pacific, (n = 110) and non-Māori/non-Pacific (n = 110) participants would provide nearly 80% power for the sub-group analysis under the same assumptions.

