### Recruitment of indigenous and ethnic minority populations

Researchers have typically struggled to recruit sufficient participants from indigenous and ethnic minority populations to allow for sub-analyses to be undertaken by ethnicity. The eGAME study aims to recruit equal numbers of Māori, Pacific, and nMnP participants, and proactive steps were taken to maximize recruitment in Māori and Pacific populations.

Consultation with Māori and Pacific communities during the focus groups provided useful feedback on design of the main study. A specialized Māori/Pacific recruiter was contracted to assist with recruitment of these populations and consult on cultural issues relevant to the conduct of the research. As a result, additional recruitment sites were set up in the greater Auckland area where a large number of Māori and Pacific resided, to improve access of these populations to the study. Furthermore, some study processes were modified to improve cultural appropriateness. For example, at one study site the screening phone call was changed to a face-to-face visit between study staff and the potential participant and their family, the preferred mode of communication for Māori and Pacific populations. The Māori/Pacific recruiter maintained regular contact with participants throughout the course of their involvement with study. Despite these steps, recruitment of Māori and Pacific children remains a challenge. At the time of submission of this manuscript, the eGAME sample comprised 17% Māori and 27% Pacific participants, below the target of 33% for each.

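### The ethnic sub-group analysis is premised on roughly equal groups of 110, but the article reports an interim mix of 17% Māori and 27% Pacific and does not revise the sub-group text

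*Protocol article*

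**What the plan says.** Three places in the protocol article bear on this.

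- **Sample size.** The trial is sized at 330 for a BMI difference of 0.8 kg/m², "assuming a standard deviation (SD) of 2.0 kg/m^2" and "allowing for 20% loss to follow up". The sub-group sizing follows: "Recruitment of equal numbers of Māori (indigenous people) (n = 110), Pacific, (n = 110) and non-Māori/non-Pacific (n = 110") is said to give nearly 80% power for the sub-group analysis under the same assumptions.
- **Statistical analysis.** "With roughly equal number of Māori, Pacific and non-Māori non-Pacific participants, appropriate sub-group analysis will be carried out for each ethnicity". The sentence goes on to make this conditional on a significant overall treatment effect.
- **Discussion, Recruitment of indigenous and ethnic minority populations.** When the manuscript was submitted, "the eGAME sample comprised 17% Māori and 27% Pacific participants, below the target of 33% for each". This was despite a dedicated recruiter, added sites and modified procedures, and the section says recruitment of these children is still difficult. It gives the wish to analyse by ethnicity as the reason for seeking equal numbers. It does not say how many children had been enrolled.

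No section changes the sub-group analysis or its sizing in the light of the reported mix.

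**The concern.** The analysis text takes as its premise a balance that the same article reports is not being achieved. If the imbalance lasts, the three separate analyses will carry very different amounts of information, least of all in Māori children. The article states no caution about this. Three separate tests at 5%, one on a large group and two on small ones, can differ in significance when the effect is the same in all three. A reader could take such a result to mean that the intervention does not work in Māori or Pacific children, the groups for whom equal recruitment was sought.

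**Working it through.** **Inputs.** From Sample size: N = 330, difference 0.8 kg/m², SD 2.0 kg/m², two-sided 5%, 20% loss, 110 per ethnic group. From the Discussion: 17% Māori and 27% Pacific, hence 100 − 17 − 27 = 56% non-Māori/non-Pacific (nMnP). Assumed: 1:1 allocation (ratio not stated), also within each ethnic group, since randomization is stratified by ethnicity.

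**The plan's own figures.**
- Overall: n per arm = 2 × (1.960 + 1.282)² × (2.0/0.8)² ≈ 132, so 264 in total, and 264/0.8 = 330. The overall size reproduces exactly.
- Sub-groups at 110 each: 55 per arm, or 44 after loss. The two-sample t-test (noncentral t, standardized difference 0.8/2.0 = 0.4) has power 55% without loss and 46% after it. The stated figure of nearly 80% therefore does not reproduce for BMI even at the target. That is a separate fault; the question here is what the mix adds.

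**Projected group sizes if the mix persists.** 330 × 0.17 = 56.1; 330 × 0.27 = 89.1; 330 × 0.56 = 184.8.

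**Power and precision.** Half-width = 1.96 × 2.0 × √(2/n), with n the number per arm after 20% loss.

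| Group | Enrolled | n per arm after loss | Power after loss | Power, no loss | 95% CI half-width (kg/m²) |
|---|---|---|---|---|---|
| Māori | 56 | 22.4 | 26% | 31% | 1.17 |
| Pacific | 89 | 35.6 | 38% | 46% | 0.93 |
| nMnP | 185 | 73.9 | 68% | 77% | 0.64 |
| Equal groups | 110 | 44 | 46% | 55% | 0.84 |

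Relative to equal groups, the mix costs Māori about 46 − 26 = 20 points and Pacific about 46 − 38 = 8 points from the rounded figures (7 unrounded: 45.8 − 38.4 = 7.4).

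**Allowing for the condition on the overall effect.** Sub-group tests are run only after a significant overall result. Simulating a uniform 0.8 effect at this mix and keeping only trials with a significant overall test, power is about 29%, 43% and 74%. These use a normal approximation; a repeat with t-tests gave 28%, 42% and 74%.

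**Patterns of significance.** Without the condition, the chance that nMnP alone is significant is 0.676 × (1 − 0.258) × (1 − 0.384) = 0.676 × 0.742 × 0.616 = 31%. With the condition it is about 32%, the most frequent of the eight possible patterns. All three are significant in about 8%.

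**How far the projection could move.** Equal groups of 110 within 330 remain possible only if the nMnP count has not passed 110: 0.56 × n ≤ 110, so n ≤ 196. At n = 196 there would be about 33 Māori and 53 Pacific children, and the other 134 places would all have to go to Māori (77) and Pacific (57) children. Between a mix that persists and one that is fully corrected, power after loss runs from 26% to 46% for Māori, 38% to 46% for Pacific and 68% to 46% for nMnP.

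**The case against.** The strongest reply is that this is an open progress report beside a statement of intent. The mix is dated to manuscript submission, recruitment was continuing and the aim of equal numbers was still held. The Sample size sentence is conditional: equal recruitment would provide the power. The analysis sentence can likewise be read as making balance a condition. How sub-group results are worded is often left to a fuller plan, which is not shown. Most of this stands as a limit on the point. It does not remove the mismatch, because the article itself states the premise and the sizing and then reports facts against both.

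Three stronger readings are tempting and should not be made.

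- *That the groups analysed will be 56 and 89.* These are projections. Enrolment at submission is not given, and 110 each is still attainable if no more than about 196 children had been enrolled.
- *That the trial would most likely find an effect only in the nMnP group.* That is the commonest single pattern, but at about 32% it fails to occur roughly two times in three. The condition on the overall effect also means that any sub-group result would sit beside a positive overall one, which tempers a reading of failure without ruling it out.
- *That the mix is the main cause of weak sub-group power.* Equal groups of 110 would themselves give only about 46% after loss, and all three would be significant only about 11% of the time given a significant overall effect. The mix adds a substantial loss for Māori children and a small one for Pacific children.

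**Conclusion.** The point holds as an unreconciled mismatch within the article. The sub-group analysis is premised on, and sized for, equal groups that enrolment was not delivering when the article was submitted. Its practical weight is greatest for Māori children, where the interval would be about ±1.2 kg/m² around an effect of 0.8. The figures rest on the reported mix persisting to 330, 1:1 allocation within groups, 20% loss spread evenly, the article's SD of 2.0 and a simple two-group comparison. The primary comparison and its sample size are unaffected. The correction should be made before results are seen; the article expects them in early 2010.

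**What to change.** - **Statistical analysis:** remove the premise of roughly equal numbers. Keep the condition on the overall effect. State that sub-group results will be given as estimates with 95% confidence intervals, alongside a treatment-by-ethnicity interaction estimate, and that a non-significant result in one group will not be read as no effect there. The interaction estimate addresses directly whether the effect differs between groups, which separate tests do not.
- **Sample size:** keep 110 per group on record as the original aim. Add that enrolment is falling short of it and that the sub-group power statement does not apply to the mix being enrolled. Give the projected sizes (about 56, 89 and 185) and half-widths (about 1.2, 0.9 and 0.6 kg/m²), labelled as projections to be updated when recruitment ends.

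The cost is wording and a less favourable statement of sub-group precision. No extra recruitment is needed.

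### Sub-group analysis within each ethnicity, run only after a significant overall effect, cannot show whether the effect differs by ethnicity, and its within-group power is about 47%, not nearly 80%

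*Protocol article*

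**What the plan says.** Under Statistical analysis, the article describes a repeated-measures mixed model for change from baseline at 12 and 24 weeks. Ethnicity enters as an adjustment covariate, alongside the baseline value, age and sex. On testing: "All statistical tests will be two-tailed and a 5% significance level maintained throughout the analyses". The rule for sub-groups is that "appropriate sub-group analysis will be carried out for each ethnicity if there is a significant overall treatment effect". The same sentence opens with a premise about numbers: "With roughly equal number of Māori, Pacific and non-Māori non-Pacific participants". No treatment-by-ethnicity interaction or heterogeneity test is named.

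Under Sample size: "A sample size of 330 participants was estimated to provide at least 90% power" for a 0.8 kg/m² "difference in change in BMI from baseline to the end of intervention period between the two groups", with SD 2.0 kg/m² "and allowing for 20% loss to follow up". The same section says that 110 children in each of three ethnic groups would give close to 80% power for the sub-group analysis on unchanged assumptions. That is a statement about detecting the treatment effect inside a group of 110, so it indicates that within-group tests are intended.

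Under Recruitment of indigenous and ethnic minority populations, the article reports that at submission "the eGAME sample comprised 17% Māori and 27% Pacific participants, below the target of 33% for each".

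**The concern.** Whether the intervention works in a given group and whether it works differently across groups are separate questions. Three separate tests address the first, with a third of the data each. They do not address the second: a significant result in one group beside a non-significant result in another is what sample size and chance commonly produce when the true effect is identical.

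This matters here because the trial set equal ethnic targets and took active recruitment steps so that results by ethnicity could be given. If groups end up unequal, a pattern of significance in the largest group and not in the smallest is the likeliest mixed result under a uniform effect, and it invites a wrong inference about the children the design set out to inform.

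The gate adds a second weakness. Effects that run in opposite directions and cancel overall would seldom trigger the sub-group analysis.

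**Working it through.** **Inputs.** From Sample size: effect δ = 0.8, SD = 2.0, two-sided 5%, 330 randomized, 20% loss, 110 per ethnic group. From the recruitment section: 17% Māori and 27% Pacific, hence 56% non-Māori/non-Pacific (nMnP) by subtraction. Assumed: 1:1 allocation (not stated, but it reproduces 330), and equal SD and uniform loss across groups.

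**Formula.** With n analysed per arm, SE = SD × √(2/n) and power = Φ(δ/SE − 1.96).

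**1. Overall figure.** 330 × 0.8 = 264, so n = 132 per arm. SE = 2 × √(2/132) = 0.246; 0.8/0.246 = 3.25; power = Φ(1.29) = 90.1%. The stated 90% reproduces.

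**2. One ethnic group of 110.** 55 per arm randomized, 44 after loss. SE = 2 × √(2/44) = 0.426; 0.8/0.426 = 1.876; power = Φ(−0.084) = 46.7%. With no loss (n = 55) it is 55.5%. The stated figure does not reproduce for BMI. It would need 99 analysed per arm (248 randomized per ethnic group), or an SD of about 1.34 at 44 per arm. For fitness (SD 7, 44 per arm), power is 52%, 76% and 92% at 3, 4 and 5 ml/kg/min, so the figure is approached only near the middle of that range.

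**3. Uniform true effect of 0.8, equal groups.** The three groups are independent, so all three are significant with probability 0.467³ = 0.102. If all three are significant, the overall test is too. Given overall significance:
- P(at least one non-significant) = 1 − 0.102/0.901 = 0.887. Simulation with 2,000,000 runs gives 88.8%.
- One or two groups significant: 79.7%. No group significant: 9.0%.
- With no loss, at least one is non-significant in 82.1%.

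**4. Same, if the mix at submission were final.** Analysed per arm: 0.17, 0.27 and 0.56 × 132 = 22.4, 35.6 and 73.9. Within-group power is 26.7%, 39.3% and 68.1%. The product is 0.0716, and 1 − 0.0716/0.9015 = 0.921. Given overall significance, simulation puts the non-significant share at 71% for Māori, 57% for Pacific and 26% for nMnP.

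**5. How much is due to low power.** If within-group power really were 80%, the figure in step 3 would be 1 − 0.8³ = 48.8%.

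**6. The interaction test.** Under a uniform effect, a 2-df test signals a difference in 5.0% of trials with a significant overall result. Its power is modest. Each group has weight 1/SE² = 44/(2 × 2.0²) = 5.5. For effects 0/0.8/0.8 (mean 0.533), the noncentrality is 5.5 × (0.533² + 2 × 0.267²) = 2.35, giving about 26%.

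**7. The gate.** For effects −0.8/0/+0.8 in equal groups, the overall true effect is zero, so the two-sided 5% gate opens in about 5% of trials. The noncentrality is 5.5 × 1.28 = 7.04, so an ungated interaction test would detect this pattern in about 66%.

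**The case against.** The strongest objection is that a condensed article need not name the sub-group method. It promises an appropriate analysis, and an analysis plan that is not shown may contain an interaction test. A reader might infer that the trial has no such test; the article does not support that. What stands is narrower: the per-ethnicity unit, the trigger and the power basis are all printed, and they describe within-group testing.

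Second, a reader might infer that the trial would conclude that the games do not work in Māori children. Nothing says that a non-significant sub-group will be read as no effect, or that groups will be compared by significance. An effect for each group is a legitimate aim, and an estimate with its interval would not mislead in this way. The figures show how easily such a misreading could arise, not that it will be made.

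Third, much of the 89% reflects low within-group power. That is correct: at a true 80% it falls to about 49%. This makes the power statement part of the problem; it does not remove it.

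Fourth, the 17/27/56% mix is the position at submission, and the article still aims for equal numbers. The 92%, 71% and 26% therefore hold only if that mix persists. The equal-numbers phrase may also be read as a condition for doing the analysis at all.

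Fifth, gating is a recognised guard against chasing sub-groups after a null result. That is fair for within-group claims. It would be too strong to say that opposing effects would never be examined, since exploratory work is not barred and nothing suggests such effects; rarely is the right word.

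**Conclusion.** The point holds in this limited form. The stated rule tests the effect inside each ethnic group after a significant overall result, and that cannot establish whether the effect differs by ethnicity. Under a uniform 0.8 kg/m² effect, at least one group would be non-significant in about 89% of trials that pass the gate (82% with no loss; about 92% if the mix at submission persisted). An interaction test would falsely signal a difference in 5%. For BMI, within-group power is about 47% with loss and 55.5% without, so the stated sub-group power does not follow from the article's assumptions.

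These figures rest on SD 2.0 in every group, 1:1 allocation, uniform loss and a normal approximation. A smaller residual SD after baseline adjustment would raise within-group power, but the article gives no such value. The analysis is secondary, so the overall primary comparison is unaffected.

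**What to change.** - Add a treatment-by-ethnicity interaction to the primary mixed model. Report it whatever the overall p-value, and base any claim that effects differ by ethnicity on it.
- From that model, report ethnicity-specific estimates with 95% CIs at 12 and 24 weeks, matching the outcome definition, and label them descriptive. State that ethnic groups will not be compared by whether each is significant.
- Restate the sub-group power: about 47% for BMI at 110 per group with 20% loss.
- Describe equal ethnic numbers as a target, and do not present them as an established premise of the analysis.

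I would not go further and bar within-group claims unless heterogeneity is shown. That would make Māori- and Pacific-specific results depend on a test with little power.

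The cost is wording and one interaction in the model. Ethnicity is already a stratification factor and a covariate, so no new data are needed. The downside is the interaction test's low power, about 26% if one group has no effect and two have 0.8. The plan should say so, so that a non-significant interaction is not taken as evidence of equal effects.

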## Discussion

A number of reflections on study design and conduct arising from this RCT are likely to be of interest to those undertaking similar work.

### Determining the feasibility of conducting such a trial

The feasibility studies [32,33] were critical to inform the design of the main study. The focus groups gave insight into the video game preferences of children; in particular, it was identified that older children preferred traditional non-active gaming, and thus were unlikely to be complaint to an active video games intervention. The researchers therefore tailored the intervention to an appropriate age group (10–14 years) for the main trial. Also, parents generally supported the concept of active video gaming, and would therefore be more likely to promote home use of the games. The energy expenditure study provided information specific to the gaming system of interest (Sony EyeToy™), gave insight into whether the active games were sufficiently vigorous such that they could be used as a physical activity intervention, and gave an indication of how much game play may be used to cause an appreciable change in body composition.

The pilot RCT identified a myriad of issues relevant to the design and conduct of the main trial. Potential compliance problems were identified; the effect of the intervention decreased from six to 12 weeks, which raised issues of sustained interest in the intervention. For this reason, the introduction of new games was staggered throughout the intervention in the main trial to maintain interest. The pilot RCT also allowed the researchers the opportunity to develop and test the study materials and protocols on a small scale prior to the main trial. In particular, issues relating to management of the accelerometer data were resolved, such as the appropriate epoch and data reduction protocols, and systems put in place for the management of larger amounts of data. A new snack log was developed that was more appropriate to the age group than the instrument used in the pilot trial. Feasibility of recruitment processes was tested; recruitment was 100% for all three phases, with good representation by Māori and Pacific peoples.

### Developing a relationship with a corporate

Working relationships were developed with SCEE and SCENZ. SCEE provided Sony EyeToy cameras and games for study participants. However, their involvement posed a potential conflict of interest; therefore, the roles and responsibilities of both the corporate and academic parties were clearly outlined in a formal agreement prior to the start of the study. Funding for the study was secured from a national health research funding body, and SCEE did not contribute to the design, conduct or analysis of the research.

### Working with schools to conduct research

The primary mode of recruitment has been through schools. Therefore, developing and maintaining an effective working relationship with schools is crucial to the success of the project. The participation of schools in research is voluntary and in the past has often involved significant disruption to the school timetable and the requirement of staff time to help co-ordinate data collection. Furthermore, there is no common method to approach schools, which has resulted in school principals fielding scores of requests from researchers weekly. This has resulted in a somewhat strained relationship between schools and the academic community and an increasing reluctance for schools to be involved in research. The eGAME recruitment strategy sought to minimize disruption to school processes. With the principal's permission, a 5–10 minute presentation was scheduled during a regular school assembly slot. In this presentation, a brief outline of the study was given and interested students wrote their contact details on forms distributed to classes. Approximately seven days later, these forms were collected from the school. Potential participants and their parents were then contacted outside of school hours for screening. All assessments took place in the evening or weekend so as not to disrupt school attendance. Researchers seeking to undertake research with school involvement should aim to minimize the use of school time and resources where possible. Furthermore, researchers should keep schools up to date with relevant information and the results of the trial once completed.

